#### Construct Validity

Construct validity will be assessed using exploratory factor analysis (EFA). Based on the recommended participant-to-item ratio of at least 5:1, a minimum of 330 participants is required, with an additional 10% to account for potential attrition, yielding a total target sample of 363 participants. EFA will be performed to evaluate the underlying factor structure and to determine whether the items load appropriately onto the intended domains [36,37]. Participants will be recruited through convenience sampling from the Geriatric Clinic at Universiti Malaya Medical Center (UMMC), Kuala Lumpur, and Hospital Kuala Lumpur. This sample size is expected to provide adequate power and stability for robust factor extraction and model interpretation.

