### Sample Size Calculation

The sample size for Phase 2 was calculated for comparison of 2 independent means (intervention vs control) assuming equal group sizes, a 2-sided test with a significance level of *α*=.05, and power (1−β)=0.80. The calculation followed the method described by Rosner [43] and Turnbull et al [44]. The required sample size per group was obtained using the formula:

$$n=\frac{(\sigma_{1}^{2}+\sigma_{2}^{2})(Z_{1-\alpha /2}+Z_{1-\beta }{)}^{2}}{\Delta^{2}}$$

where $\sigma_{1}$ and $\sigma_{2}$ are the SDs in the 2 groups, $Z_{1-\alpha /2}$ is the standard normal deviate at the 5% (1.96) significance level, $Z_{1-\beta }$ is the standard normal deviate for 80% (0.84) power, and Δ is the expected mean difference between the groups.

Based on Turnbull et al [44], an expected mean difference in knowledge scores of 1.69 was used, with SDs of 2.53 and 2.76, respectively. Substituting these values:

$$n=\frac{(2.53^{2}+2.76^{2})(1.96+0.842{)}^{2}}{1.69^{2}}\approx 38.5$$

Thus, approximately 39 participants are required per group. To account for an anticipated 30% attrition rate, the sample size was inflated:

$$n_{\text{adjusted}}=38.5\times 1.30\approx 50$$

Accordingly, 50 participants will be recruited into each arm (intervention and control), giving a total sample size of 100 caregivers.

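### The 30% attrition allowance multiplies by 1.30 instead of dividing by 0.70, so 50 per arm leaves 35 and about 76% power under the plan's own formula, not 80%

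*Protocol article*

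**What the plan says.** All of the Phase 2 inputs are in the Protocol article, under Sample Size Calculation. The comparison is of two independent means, "assuming equal group sizes", with "a 2-sided test with a significance level of *α*=.05" "and power (1−β)=0.80". The effect and variability come from a cited study: "an expected mean difference in knowledge scores of 1.69 was used, with SDs of 2.53 and 2.76, respectively". The formula gives 38.5, and the text concludes: "Thus, approximately 39 participants are required per group".

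The attrition step follows: "To account for an anticipated 30% attrition rate, the sample size was inflated". The printed calculation multiplies 38.5 by 1.30 and arrives at about 50. The recruitment target is then fixed: "Accordingly, 50 participants will be recruited into each arm (intervention and control), giving a total sample size of 100 caregivers". The Abstract repeats the total of 100.

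**The concern.** An attrition rate is ordinarily a share of the people enrolled. If 30% of those enrolled are lost, 70% remain, so the number to recruit is the required evaluable number divided by 0.70. Adding 30% to the required number is a different operation and always gives too few.

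This matters because it is the only sample size justification given for Phase 2. As written, a reader would take it that 80% power survives the 30% loss the authors expect, and the section's own numbers contradict that. The loss is also a scenario the article takes seriously. The Discussion names retention in Phase 2 as a likely difficulty, and the missing-data section plans for more than 20% of outcome data being absent.

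**Working it through.** **Inputs** (all from Sample Size Calculation): difference Δ = 1.69; SDs 2.53 and 2.76; two-sided α = .05 (1.96); power 0.80 (0.842 in the substituted formula); equal arms; attrition 30%; 50 recruited per arm.

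**1. Reproduce the base figure.**
- Sum of variances: 2.53² + 2.76² = 6.4009 + 7.6176 = 14.0185.
- n = 14.0185 × (1.96 + 0.842)² / 1.69² = 14.0185 × 7.8512 / 2.8561 = 38.54.
- This matches the stated 38.5, rounded up to 39 per arm. The base calculation is sound.

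**2. Reproduce the inflated figure.**
- 38.5 × 1.30 = 50.05, the stated 50.
- Division gives something else: 38.5 / 0.70 = 55.0, and 39 / 0.70 = 55.7, rounded up to 56. The target of 50 comes only from multiplication.

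**3. Apply the stated attrition to the stated target.**
- 50 × 0.70 = 35 per arm, which is 39 − 35 = 4 below the requirement.
- By comparison, 55 × 0.70 = 38.5 and 56 × 0.70 = 39.2.

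**4. Power at what remains, by the plan's own formula.**
- At 35 per arm: 1.69 / √(14.0185/35) = 2.670; 2.670 − 1.96 = 0.710; Φ(0.710) = 0.761.
- At 39 per arm the same calculation gives 0.805.

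| Evaluable per arm | Power, normal | Power, noncentral t |
|---|---|---|
| 35 | 76.1% | 74.9% |
| 39 | 80.5% | 79.5% |

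Compared like with like, the drop is 80.5 − 76.1 = 4.4 points (normal) or 79.5 − 74.9 = 4.6 points (t), from rounded figures. The chance of missing a true difference of 1.69 is about 24% (100 − 76.1), not the 20% planned.

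**5. Attrition that 50 per arm can absorb.**
- 1 − 39/50 = 22%, or 1 − 38.5/50 = 23% from the unrounded requirement. Both are well below 30%.

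**The case against.** **The planned analysis is not the simple formula.** The primary model is a GEE that adjusts for the baseline score and uses all available repeated measurements. A caregiver lost after the 1-month visit still contributes, and baseline adjustment can recover precision. As an illustration only, assume a baseline-outcome correlation of 0.3, which the article does not give. Then 35 per arm is worth about 35 / (1 − 0.3²) = 38.5, close to 80% power. This objection stands as a limit on the claim: 76% describes the formula used for planning, not the GEE. It does not rescue the section, which claims no such gain and relies on an explicit attrition allowance that falls short of its purpose. There is also a consideration the other way. Allocation is by hospital, two per arm, while the formula treats caregivers as independent. Neither 76% nor 80% is therefore an unconditional property of the trial.

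**The gap is modest.** It is four people per arm after attrition and a little over 4 points of power. That is fair, and it makes the point moderate, but the difference is too large to be rounding.

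**Fifty-six is not the only corrected number.** Also fair: the plan inflates the unrounded 38.5, and on that basis division gives 55.

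**A reader might extend the point to Phase 1.** Under Construct Validity the article says "a minimum of 330 participants is required, with an additional 10% to account for potential attrition, yielding a total target sample of 363 participants". Adding 10% again multiplies where it should divide, but 363 × 0.90 = 326.7, about three people short against a rule-of-thumb ratio, which is trivial. A reader might also note that 330 / 5 = 66 = 21 + 20 + 25, the items of the knowledge, attitude and practice scales. Counting the 12 burden items would give 78 items, hence 78 × 5 = 390 participants, or 390 / 0.90 = 433.3, so 434 recruited. The documents do not support that conclusion. They never say which scales enter the factor analysis or whether items are pooled. The Phase 1 overview ties validation to the KAP questionnaires, and the outcome section says the burden scale was translated into Malay in 2023. The Abstract and the Phase 1 results section, however, include burden. If each instrument is factored separately, even the longest (25 items) has 330 / 25 = 13.2 participants per item.

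**Conclusion.** The Phase 2 attrition step is wrong as written. With 50 recruited per arm and the anticipated 30% lost, 35 remain against a requirement of about 39. Power under the section's own formula is then about 76% (75% by t) rather than 80%. The size is moderate, and the base calculation of 39 per arm is correct.

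The conclusion rests on the article's own difference, SDs, two-sided 5% level and attrition rate, on independent caregivers, and on an unadjusted comparison of completers. It does not show that the planned GEE will have less than 80% power. Nor does it establish a sample size error in Phase 1, where the most that can be asked for is a clarification.

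**What to change.** Keep 50 per arm and replace the attrition sentence and its formula with a statement of this kind:

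> Under the two-independent-means formula, assuming independent caregivers, 30% attrition leaves 35 per arm and about 76% power for a difference of 1.69; 80% power under this formula is kept for attrition up to about 22%.

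This changes wording only. The cost is that a stated figure becomes slightly less favourable.

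If the sponsor would rather preserve 80% power at 30% attrition under the same formula, division by 0.70 gives 55 per arm (110 in total, from 38.5) or 56 per arm (112 in total, from 39). That means 10 to 12 more caregivers than the stated 100. The article reports that Phase 2 had not started when it was submitted.

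For Phase 1, no new number is needed. At most, the sponsor could state which scales the 5:1 ratio covers and whether it applies to each instrument separately.

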### Study Outcome

The outcomes of this study will be evaluated using validated instruments measuring caregivers’ KAP and burden level in relation to caring for people living with dementia.

#### Knowledge

Caregiver knowledge will be assessed using the DKAT-2, developed by Toye and colleagues [22] at Curtin University. The DKAT-2 consists of 21 items with Yes/No/Don’t Know response options and measures understanding of the dementia trajectory and evidence-based care approaches. Each item is scored as correct or incorrect, with “Don’t Know” categorized as incorrect. Total scores reflect overall knowledge, with higher scores indicating greater understanding of dementia care. The DKAT-2 demonstrates strong psychometric performance, including high internal consistency (Cronbach *α*=0.79), supporting its use in evaluating caregiver education and guiding patient-centered interventions [22].

#### Attitude

Attitudes toward dementia will be measured using the DAS, developed by O’Connor and McFadden [23]. The DAS comprises 20 items rated on a 7-point Likert scale (1=strongly disagree to 7=strongly agree), capturing cognitive, emotional, and behavioral components of attitudes toward dementia. Higher scores denote more positive attitudes. The scale has demonstrated excellent reliability (Cronbach *α*=.83‐.85) and a stable 2-factor structure confirmed through exploratory and confirmatory factor analyses [23]. Its broad conceptual coverage makes it suitable for evaluating the impact of educational and psychosocial interventions.

#### Practice

Caregiving practices will be assessed using the CTI-25. The CTI-25 is a shortened and refined version of the original 45-item instrument developed by Clark and Rakowski in 1983 [24], with improvements introduced by Lee and Mok [25] to enhance clarity and reduce redundancy. The instrument contains 25 items across 5 domains: learning to cope with a new role; providing care based on the care recipient’s needs; managing one’s emotional needs; appraising supportive resources; and balancing personal and caregiving demands.

Items are rated on a 3-point Likert scale (0‐2), with higher scores reflecting greater caregiving difficulty. The CTI-25 demonstrates strong psychometric properties, including high internal consistency (*α*=.93) and construct validity supported by confirmatory factor analysis [25].

#### Burden Level

Caregiver burden will be measured using the ZBI-12, a validated abbreviated version of the original 22-item ZBI developed by Zarit in 1980 [26-28]. The ZBI-12, translated into Malay in 2023, evaluates key burden domains including privacy, social life impact, emotional strain, health effects, and time-related pressures. The shorter format enables rapid screening and ongoing monitoring while retaining strong psychometric performance. Total scores are categorized as: 0‐10 (no to mild burden); 11‐20 (mild to moderate burden); and 20 or more (high burden) [26-28].

### Harms and Safety Monitoring

This study evaluates an educational mHealth app and standard health education materials, which are considered minimal-risk behavioral interventions. No physical risks are anticipated. Harms will therefore be defined as any self-reported serious psychological distress or any adverse event that participants or clinicians consider to be related to use of the app or study procedures. At each follow-up contact, participants will be asked whether they experienced any problems or distress related to the intervention or study participation. Participants may discontinue app use or withdraw from the study at any time on request, without consequences for their routine care. Any serious adverse events judged to be related to the study will be reported to the relevant ethics committees in accordance with institutional policies.

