### Study Population

The target population is dementia caregivers in Malaysia, while the accessible study population comprises primary caregivers of people living with dementia aged 18 years and older in Selangor. The sampling population is caregivers of registered people living with dementia attending the study sites from December 2024 to February 2026. The sampling unit is a consenting primary caregiver providing direct care to registered people living with dementia.

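### App guidance is to be applied to the person with dementia, but follow-up does not specifically ask about events in that person and filters reports by perceived relatedness

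*Protocol article*

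**What the plan says.** The Harms and Safety Monitoring section classes both the app and the control materials as minimal-risk and states "No physical risks are anticipated". It does not say to whom this applies. From that premise it derives its definition of harm: "any self-reported serious psychological distress or any adverse event that participants or clinicians consider to be related to use of the app or study procedures". The active enquiry, made at each follow-up contact, is that "participants will be asked whether they experienced any problems or distress related to the intervention or study participation". Reporting to outside bodies is narrower still: "Any serious adverse events judged to be related to the study will be reported to the relevant ethics committees".

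The participants are caregivers. Under Study Population: "The sampling unit is a consenting primary caregiver providing direct care to registered people living with dementia". Textbox 2 requires that the person cared for be at least 60 years old. It admits any type of dementia and sets no limit on severity.

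Textbox 4 lists the app's basic content. Besides general information, it covers dietary care, oral exercise, basic exercise, and physical and memory rehabilitation for the person living with dementia. The section on engagement provides for reminders to keep using the app, weekly in the first month and every two weeks after that.

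**The concern.** The app is meant to change what caregivers do, and several of its topics are carried out on another person. Any physical consequence of that content would mostly fall on the care recipient, who is not a trial participant and does not answer the harms question. The physical-risk sentence does not address this, and the harms definition is derived from that sentence.

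What is at stake is the reading of the safety result, not the effect estimates. The Discussion foresees clinicians recommending the app in routine care, and the Conclusion expects better outcomes for people with dementia as well as for caregivers. If the trial reports that no harms were recorded, readers will tend to apply that to both members of the pair, although the enquiry was worded around only one of them.

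**Working it through.** The plan gives no figure for this point, so the main check sets the sections side by side.

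1. **Who receives the content.** In Textbox 4, diet, oral exercise, basic exercise and rehabilitation are directed at the person with dementia, through the caregiver.
2. **Who is asked.** The follow-up question goes to participants, who are caregivers (Study Population; Textbox 2), and concerns what they experienced.
3. **What counts.** The definition takes in any adverse event that a participant or clinician thinks related. It names no affected person, so an event in the care recipient is not ruled out.
4. **What filters it.** Relatedness is applied three times: in the question, in the definition and in the reporting rule. A caregiver who puts a fall down to the dementia has no prompt to mention it.
5. **Whether arms can be compared.** Events are recorded only if someone attributes them to the study, and caregivers in the two arms receive different material. The article therefore provides no attribution-free count of care-recipient events by arm, although a control arm exists.

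A second check asks how much a count could show if these events were fully ascertained. For zero events in n observed care recipients, the one-sided 95% upper bound on the true rate is 1 − 0.05^(1/n).

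- All 50 recruited per arm observed (Sample Size Calculation): 1 − 0.05^(1/50) = 0.058, or 5.8%.
- 30% attrition, the protocol's own allowance: 50 × 0.70 = 35, and 1 − 0.05^(1/35) = 0.082, or 8.2%.

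These bounds describe any arm of that size with complete ascertainment. They do not measure the gap. They show the limit of what the proposed question could deliver.

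**The case against.** The strongest reply is that the definition already reaches the care recipient and names clinicians as well as caregivers as judges of relatedness. The question is also open. A caregiver whose relative was hurt while following an app exercise could well report it as a problem related to the intervention. Both points stand. A reader might infer that care-recipient injuries are excluded, or that the questioning could never bring one out; the text supports neither.

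A reader might also infer that the app is physically hazardous. The documents do not show this. Textbox 4 gives only topic headings, the content of the modules and any cautions in them are not visible, and no event rate is stated. Falls or choking are plausible consequences of such topics, not documented ones.

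Nor is the issue confined to the app. The Ministry of Health leaflets and video also cover exercise and daily care. This is a reason to ask both arms the same question.

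Finally, the full protocol or the case report form may contain a more specific prompt, since an article condenses. This stands in part. But the article itself states the physical-risk premise, the definition built on it and the content of the follow-up enquiry, and the point rests on those statements. The Discussion makes no explicit safety claim, so the risk lies in how a null harms report would be read.

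**Conclusion.** The point holds as a gap in ascertainment. Followed as written, the plan does not specifically ask about the person to whom the exercise, oral exercise, diet and rehabilitation guidance is applied, and it keeps only events that someone considers related. Such events may be under-detected, and a report of no harms could not be taken as absence of harm to the care recipient.

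The extent of under-detection cannot be estimated, because the documents give neither a background event rate nor the module content. The primary and secondary outcome analyses are unaffected. The conclusion assumes that caregivers do apply the guidance, which is the app's stated purpose, and that the follow-up enquiry is no more specific than the article describes.

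**What to change.** Three changes in Harms and Safety Monitoring:

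1. Reconcile the physical-risk sentence with Textbox 4. It could, for example, be limited to the caregiver, or say that physical risk to the care recipient is expected to be low but will be monitored.
2. State that events in the care recipient count as harms.
3. At T1 and T2, in both arms and in the same words, add one question on whether the person cared for had a fall, injury, choking episode or unplanned medical visit, regardless of perceived cause. Report the counts by arm.

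The cost is one question at two contacts that already take place, plus the wording changes. The article says Phase 2 had not started at submission; if it has since begun, the question can still be added at the remaining follow-ups, with the date of the change reported. If the full follow-up form already has such an item, only the text needs aligning.

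The drawback is that background events unrelated to the study material will also be recorded. The identical question in the control arm puts these in context, but the arms are not randomized and the counts will be small, so they should be presented as descriptive only.

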#### Comparator (Control Arm)

Caregivers in the control arm will receive standard Ministry of Health (MOH) dementia educational materials, which are the dementia leaflets and video. These materials will be explained in detail during the baseline session to ensure consistent educational exposure and engagement comparable to that provided in the intervention arm [42].

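### Harms are elicited and, apart from serious distress, counted only when attributed to the app or study, so unattributed events go unrecorded and counts by arm may carry attribution bias

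*Protocol article*

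**What the plan says.** The section Harms and Safety Monitoring does three things.

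- It defines harms in two parts. The first is distress: "Harms will therefore be defined as any self-reported serious psychological distress". The second is "any adverse event that participants or clinicians consider to be related to use of the app or study procedures".
- It describes one way of finding them. At each follow-up contact, "participants will be asked whether they experienced any problems or distress related to the intervention or study participation".
- It sets onward reporting: "Any serious adverse events judged to be related to the study will be reported to the relevant ethics committees".

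The section begins by covering both the app and the standard education materials, and the question is not restricted to one arm. Under Comparator (Control Arm), "Caregivers in the control arm will receive standard Ministry of Health (MOH) dementia educational materials", that is, leaflets and a video and no app.

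Elsewhere, "Caregiver burden will be measured using the ZBI-12", an instrument that "evaluates key burden domains including privacy, social life impact, emotional strain, health effects, and time-related pressures". The CTI-25, described under Practice, scores caregiving difficulty and has a domain on the caregiver's own emotional needs. Both are collected in both arms at baseline, 1 month and 3 months. Under Inferential and Longitudinal Analysis, a GEE model with a group-by-time term compares them between arms.

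**The concern.** Relatedness is a judgement about cause. When it is a condition for recording an event, and not a field filled in afterwards, events that fail the test leave no trace and cannot be reassessed.

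That matters here for three reasons.

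- The harm the plan names, psychological distress, has an obvious rival explanation in caregiving itself. A caregiver or clinician looking at one case has little basis for separating the two. Comparing all events by arm is the more natural source of evidence.
- The opportunity to attribute may differ by arm. Only one arm has an app, and the second part of the definition names the app and study procedures but not the leaflets or video.
- Allocation is by hospital. The Allocation and Blinding section covers participants and those analysing the data, and does not say that clinicians who judge relatedness are blinded.

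At stake is the meaning of the harms table. A low count could reflect few events or few attributions, and a difference between arms could reflect either.

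**Working it through.** The plan gives no harms rate, threshold or power, so there is no stated figure to reproduce. The check is textual, followed by an illustration.

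**Step 1: the three filters side by side**

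| Element | Serious distress | Other adverse events |
|---|---|---|
| Definition | Counts if self-reported; no attribution needed on the natural reading | Counts only if a participant or clinician considers it related |
| Follow-up question | Asked about only if related to the intervention or participation | Same condition |
| Ethics-committee reporting | Serious events judged related | Serious events judged related |

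In the first column, definition and question disagree. Unattributed serious distress meets the definition but would surface only if volunteered. In the second column they agree, and unattributed events drop out at both steps. If the relatedness clause is instead read as applying to distress too, the disagreement disappears, but then every harm is filtered.

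**Step 2: is there another route?** No section of the article describes collecting adverse events regardless of cause. The ZBI-12 and CTI-25 are free of attribution, but they are scale scores analysed as outcomes, and the harms section does not refer to them.

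**Step 3: illustration of the effect on counts**

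Expected recorded events in an arm = n × true event rate × probability of attribution.

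Input from the document: n = 50 per arm (Sample Size Calculation). The rates and attribution probabilities are assumptions, chosen to show the range.

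| True rate, app v control | True events | Attribution, app v control | Recorded |
|---|---|---|---|
| 20% v 20% | 10 v 10 | 50% v 10% | 10 × 0.5 = 5 v 10 × 0.1 = 1 |
| 20% v 20% | 10 v 10 | 10% v 50% | 1 v 5 |
| 20% v 20% | 10 v 10 | 20% v 20% | 2 v 2 |
| 30% v 10% | 15 v 5 | 10% v 10% | 1.5 v 0.5 |
| 30% v 10% | 15 v 5 | 10% v 50% | 15 × 0.1 = 1.5 v 5 × 0.5 = 2.5 |

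Equal attribution keeps the ratio between arms but shrinks the counts. Unequal attribution can create a difference where there is none (rows 1 and 2) or reverse a real one (row 5). The direction cannot be predicted from the document.

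**Step 4: what full capture would give.** Suppose a true doubling, 10 of 50 versus 5 of 50, were fully recorded. Fisher's exact test gives p = 0.26. Power to detect 20% versus 10% with 50 per arm at two-sided 5% is about 19% by Fisher's test and 29% by the normal approximation. Unfiltered counts remove the attribution problem but do not give a confirmatory comparison.

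**The case against.** There is a good case that the matter is smaller than it looks, and much of it stands.

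- **Worsening is measured without attribution.** A rise in average burden in the app arm is something the planned two-sided GEE could show. A reader might infer that any worsening not blamed on the app is missed, or that the arms cannot be compared at all. The document supports neither. What remains is that average scores can hide deterioration in a few people, do not capture other adverse events, and are not treated as harms data.
- **Control-arm harms can be recorded.** The wording extends to study procedures and study participation. A reader might infer that the definition cannot apply to controls; it can, although without an app to point to.
- **Differential attribution is not demonstrated.** Participants are not told their allocation and are told only that they will receive education material. The attribution rates above are assumed. The bias is therefore possible, not established.
- **The background rate of distress is unknown.** The Introduction cites a Malaysian figure of 69.4%, but that is the prevalence of caregiver burden. It should not be read as the rate of serious psychological distress.
- **The article may paraphrase the question.** Exact wording may sit in a form that is not shown. The article nevertheless states the restriction, in the question as in the definition, so it is the rule as published.
- **Proportionality.** The trial compares an educational app with leaflets and a video. Minimal risk is stated as a premise, and no comparative safety objective is set. Targeted harms collection is defensible for such a trial. This argues for a light remedy, and the one below is light.

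**Conclusion.** The point holds in limited form. As written, the plan asks only about study-related problems or distress, which is narrower than its own definition of harm, and it counts other adverse events only when someone attributes them. Unattributed events are not recorded, and event counts by arm carry possible attribution bias from caregivers and from clinicians whose blinding is not described.

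The size cannot be fixed from the document. Under the assumed inputs, the recorded counts range from a false excess in either arm (5 v 1 or 1 v 5 when the truth is 10 v 10) to a reversed difference (1.5 v 2.5 when the truth is 15 v 5). With equal attribution the ratio is preserved and only the counts shrink.

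The conclusion rests on reading the harms section as the complete description of harms collection; nothing else in the article contradicts that. It does not extend to the burden and practice outcomes, which are compared between arms irrespective of cause. This is an inexpensive improvement to the harms data and does not threaten the effectiveness analysis.

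**What to change.** In Harms and Safety Monitoring:

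1. At 1 and 3 months, ask both arms, in identical neutral words, about any serious distress or other adverse event since the last contact, regardless of cause. Bring the definition into line with that question.
2. Record relatedness afterwards as a separate field, noting whether the participant or a clinician made the judgement.
3. Report all events and related events by arm, descriptively.
4. Leave ethics-committee reporting as it stands.
5. When reporting harms, refer to the planned GEE comparison of burden. Do not add a count of caregivers whose ZBI-12 score rose by any amount. Without a threshold, a one-point rise would count, and the plan accepts a test-retest reliability as low as 0.75, so many such rises would be noise.

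The cost is one reworded question, one reworded definition, one extra field and one table. More background events will have to be recorded among 100 caregivers, and comparisons at 50 per arm will remain imprecise. The article says Phase 2 had not started at submission. If follow-up has since begun, make the change in both arms on the same date and record that date.
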